**R = Randomisation**

**X = intervention**

### Participants

It is envisaged that the final sample will consist of approximately 60 children; 30 children in the IIG and 30 children in the DIG who attend Grades 4–7 (aged 9–13 years) at two schools (School 1 and School 2), for children with visual impairments in the Western Cape Province of South Africa. Letters explaining the study will be sent to the two identified schools, and the necessary written consent for participation will be requested from the school principals and school governing bodies.

Parents or guardians of the identified participants (children attending Grades 4–7) will be provided with an information letter explaining the study and a consent form giving their child permission to take part. Identified participants will also be provided with information about the study and they will be required to give written assent before they are delivered the programme. Thus, dual parent-child consent and assent will be required for inclusion. This study received approval (HS888/2013) from the Research Ethics Committee: Human Research (Humaniora) at the Stellenbosch University (Institutional Review Board Number: IRB0005239), and the Western Cape Education Department in South Africa (Reference: 20130507–10635).

### Inclusion criteria

The criterion for inclusion in the study will be one of universal prevention where children will be included in the programme regardless of their anxiety status. Universal prevention is a positive approach to social-emotional learning as it aims to build strengths in all children through the enhancement of known skills and protective factors (Farrell & Barrett 2007). However, a distinction about the programme description can be made. Based on each participants T-score on the RCADS (Chorpita *et al.*
2000) at T1, the programme can be described as either an early intervention (T-score above 65) or prevention programme (absence of significant symptoms of anxiety). Furthermore, participants should be aged between 9 and 13 (attend Grades 4–7), and be able to read and write. The reason for this requirement is that the measuring instruments are self-report surveys and participants must read the questions and complete these themselves. Lastly, with the exception of visual impairment, participants included in the study should have no other disability.

### Randomisation

Randomisation will be applied within schools with an immediate intervention and delayed intervention group within each school. Participants will be assigned to either the IIG or the DIG at their respective schools. The IIGs from School 1 and School 2 will be combined to form one large IIG, and the DIGs from School 1 and School 2 will be combined to form one large DIG.

## Programme intervention

A specifically tailored, group-based, anxiety intervention programme for children with visual impairments will be implemented as a universal intervention. The anxiety intervention programme, which is based on a CBT model, was developed over a period of six months. CBT-based interventions employ both cognitive (e.g. positive self-talk) and behavioural (e.g. relaxation) techniques to modify cognitions, behaviour and affect (Kendall 1993; Nevid, Rathus & Green 2000; Silverman & Kurtines 1996). Thus, CBT-based interventions aim to teach children to identify maladaptive thoughts and to replace these thoughts with more positive ones (Mash & Wolf 2005). In addition, one of the greatest benefits of CBT is its longevity, as CBT is focussed on equipping people with a set of coping skills that can be used both now and in the future. Furthermore, CBT-based interventions are usually shorter-term interventions, making them more cost-effective and appealing (Farrell & Barrett 2007; Ollendick & King 1998; Silverman *et al.*
2008). For these reasons, CBT was the intervention modality of choice for the study.

The eight key concepts of CBT as described by Barrett and Turner (2001) are central to the anxiety intervention programme's theoretical base, and include:

recognition of the link between thoughts and feelingsidentifying feelingsrelaxation strategiescognitive restructuringattention trainingproblem-solvingself-rewardrelapse prevention.

The programme's core theme relates to the enhancement and development of skills or competencies which can be employed when confronted with difficult situations, whether they relate to fears or worries, daily hassles (e.g. struggling with a difficult homework assignment), or stressful and aversive life events (e.g. moving to a different school or facing family conflict) (Barrett & Turner 2001). In addition to incorporating the eight key concepts of CBT, the anxiety intervention programme lent and built on ideas and concepts adapted from already existing CBT-based approaches and programmes, such as:

Kendall's Coping Cat Programme (Kendall 1990)Barrett's Coping Koala Programme (Barrett 1995)Silverman and Kurtine's Transfer of control approach (Silverman & Kurtines 1996)Stallard's Think Good-Feel Good Programme (Stallard 2002)Barrett's FRIENDS For Life Programme (Barrett 2004)Rapee's Cool Kids^®^ Programme (Rapee *et al.*
2006).

The challenge in this adaptation was not only to translate the eight key concepts of CBT into a child-friendly and age-appropriate programme, aimed at combating anxiety symptoms, but also to present the programme in a format that is accessible and appealing to children with visual impairments. As an alternative to reading and colouring in pictures (which is the norm in most of the programmes to date) the adapted programme makes use of clay (and other tactile media), toys, role-plays, games, songs, narratives and other creative techniques as alternative forms of engagement. As the FRIENDS acronym is not suitable for use in the proposed study the title for the adapted intervention programme is the P& M programme (PAM = Positive & Motivating, and in Afrikaans Positief & Motiverend). Activities in the P& M programme are aimed at teaching children with visual impairments practical skills, such as: identifying feelings; relaxation skills; identifying unhelpful and helpful thoughts; and how to deal with daily problems and challenges (Stallard *et al.*
2007).

### Immediate intervention group (IIG)

All assenting children in the IIG will receive a 10–session CBT-based, group programme, each session will last approximately 60 minutes. The sessions will take place twice a week for five weeks. Groups consist of 8–10 participants. The programme will be delivered at schools during a time negotiated with the school. The Programme will start with activities that promote group cohesion and teamwork (session 1). In sessions 2 and 3 psycho-education, regarding emotions and thoughts, is given, and in session 4 bodily reactions to anxiety are addressed and relaxation exercises are introduced. Group participants are encouraged to practice these relaxation exercises throughout the duration of the programme. The next step (session 5) relates to recognising inner thoughts and the promotion of positive thinking. Session 6 introduces the concept of cognitive restructuring and introduces participants to problem solving skills. Self-evaluation and reinforcement is introduced in session 7. Sessions 8 and 9 allow for group participants to repeat and practice the new skills they have learnt, and session 10 covers relapse prevention and there is a party to celebrate the completion of the programme. At the start of the programme, parents or guardians and teachers will also be invited to attend an additional psycho-educational information session. This information session will provide an overview of the anxiety intervention programme, discuss the rationale underlying CBT-based programmes and explain the skills that children will be taught.

### Delayed intervention group (DIG)

Participants in the DIG will be delivered the same intervention programme straight after the programme has been delivered to participants in the immediate intervention group, and they will also be asked to complete three questionnaires on four occasions, together with the children in the IIG.

### Group leader (Trainer)

The programme will be delivered by the first author and a research facilitator (a post-graduate student in psychology) in either English or Afrikaans, depending on the children's language of schooling. The first author is a registered counselling psychologist with ample experience and knowledge relating to developmental psychology and CBT. The group leader will be blind to all assessment measures. The reason the first author herself will conduct the intervention is that there are no other qualified psychologists available who are visually impaired, and who are attuned to the social and cultural context of the participants.

## Programme evaluation

As mentioned above, all assenting children from School 1 and School 2 will randomly be assigned to 1 of 2 groups at their respective school (an IIG or a DIG). The IIG groups from School 1 and School 2 will be combined to form one large IIG, whilst the DIG groups from School 1 and School 2 will be combined to form one large DIG.

The evaluation phase will comprise both a quantitative and qualitative component (more information about the qualitative component is given below). For the quantitative evaluation, all assenting children in the IIG and DIG (approximately 60 participants) will be administered a short biographical questionnaire (only at T1) and three self-report questionnaires at pre (T1), post (T2), and follow-up (T3 and T4) intervention. Children in the IIG will receive the intervention programme before the children in the DIG. It is envisaged that the programme will be delivered to the two groups (the IIG and DIG) of children according to the following outline:

Initial assessment of all children, IIG and DIG (T1)Children in the IIG receive the anxiety intervention programme (5 weeks)Re-assessment of all children, IIG and DIG (T2)Children in the DIG receive the anxiety intervention programme (5 weeks)Re-assessment of all children, IIG and DIG (T3)Final assessment of all children, IIG and DIG (T4 – It will be 6 months after the children in the IIG received the intervention and 3 months after the children in the DIG received the intervention). Resulting from time constraints, where all assessments should be conducted within one academic year, there will be no 6 month follow-up for the DIG, and no wait period for the IIG.

It will be possible to measure:

The stability of the measures when untreated over time (The DIG will act as a wait-list control group using T1 and T2 comparisons)The impact of the anxiety intervention programme immediately after completion (using immediate pre and post-data from both groups – IIG [T1 and T2]; and DIG [T2 and T3])The maintenance of the effects of the anxiety intervention programme over time following intervention (IIG using T2, T3 [3 month] and T4 [6 month] comparisons, and DIG using T3 and T4 [3 month] comparisons)

The following six hypotheses are to be tested during the evaluation phase of the proposed study (four hypotheses pertain to between group effects and two hypotheses pertain to within group effects).

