## Introduction

A substantial body of literature indicating that childhood anxiety presents a serious mental health problem has now been amassed (Barrett & Turner 2001). Firstly, the literature indicates that anxiety is one of the most common forms of psychological distress reported by youth (Barrett & Sonderegger 2005; Dadds *et al.*
1997). A recent meta analytic prevalence study indicated that an average of 12.3% of school-aged children (ages 6–12) experience significant symptoms of anxiety (e.g., Costello *et al.*
2011, 2003; Heiervang *et al.*
2007; McArdle, Prosser & Kolvin 2004; Mullick & Goodman 2005; Petersen *et al.*
2006). Secondly, although experiencing transient fears and anxieties is deemed to be a normal part of development for most children; for some these experiences may intensify and persist over time, causing interferences in daily functioning (Barrett, Lock & Farrell 2005; Silverman 2011). Thirdly, the experience of childhood anxiety has been associated with a number of somatic difficulties such as fatigue, restlessness, irritability, and sleep disturbances (Beidel, Christ & Long 1991; Pina & Silverman 2004) and psychosocial impairments such as problems with peer relations, low self-esteem, immaturity, impaired academic functioning, and concentration problems (Cooley, Boyd & Gratos 2004; Farrell & Barrett 2007; Messer & Beidel 1994; Motoca, Williams & Silverman 2012). Fourthly, if left untreated, severe symptoms of anxiety can take on a chronic and unremitting course (Barrett & Turner 2004; Cole *et al.*
1998; Weems & Silverman 2013), and many adults who are diagnosed with an anxiety disorder can trace the onset of symptoms back to their childhood (Rapee & Barlow 1993). Given this suggested relationship between childhood anxiety and adult psychopathology, it is essential for symptoms of anxiety to be addressed as early as possible (Cobham 2003), and promising in this regard is the increased evidence pointing to the amenability of childhood anxiety symptoms to brief psychosocial interventions (Lowry-Webster, Barrett & Dadds 2001; Silverman, Pina & Viswesvaran 2008).

Yet, despite these promising results, research indicates that less than 20% of children who require treatment for anxiety will receive clinical intervention (Day & Roberts 1991; Olfsen *et al.*
2003), and of those who do, a large number will terminate prematurely (Kazden 1996; Pina *et al.*

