## Method

A specifically tailored CBT-based anxiety intervention for South African children with visual impairments will be evaluated in two special schools that cater for children with visual impairments. This study is set up as a randomised wait-list control group design with pre-, post-and follow-up intervention measures, with 60 participants randomly assigned to an IIG (*n* = 30) and a DIG (*n* = 30). Before implementation of the programme 10 participants from each group will be randomly selected to take part in a focus group. The focus group will be aimed at obtaining the participants’ personal inputs and to pilot certain sections of the programme before final implementation. Both of the programme's groups will receive the 10 session anxiety intervention programme**.** The participants will complete baseline (T1), post intervention (T2 for IIG and T3 for DIG) and 3 month (T3 for IIG and T4 for DIG) or 6 month (T4 only for IIG) follow-up assessments.

The research design can be represented as follows:

R  IIG T1   X  IIG T2     IIG T3  IIG T4

R  DIG T1     DIG T2  X  DIG T3   DIG T4

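### Maintenance of the programme's effects is listed as measurable, but no untreated group is observed after T2, so at T4 a kept effect cannot be separated from natural course

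*Protocol article*

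**What the plan says.** All places are in the protocol article.

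- **Programme evaluation** lists three things the trial will be able to measure. The first is stability when untreated: "The DIG will act as a wait-list control group using T1 and T2 comparisons". The second is the immediate impact, from each group's own scores before and after the programme. The third is "The maintenance of the effects of the anxiety intervention programme over time following intervention", from IIG scores at T2, T3 and T4 and DIG scores at T3 and T4.
- **Method**: "Both of the programme's groups will receive the 10 session anxiety intervention programme".
- **Delayed intervention group (DIG)**: these children "will be delivered the same intervention programme straight after the programme has been delivered to participants in the immediate intervention group".
- **Immediate intervention group (IIG)**: "The sessions will take place twice a week for five weeks".
- **Between group effects**, hypothesis 4: the T3 results on the Revised Child Anxiety and Depression Scale (RCADS) are expected to be retained at T4 in both groups.
- **Programme evaluation** also says that fitting all assessments into one academic year leaves the DIG without a 6-month follow-up and the IIG without a wait period. It does not say that follow-up has no untreated comparison.
- **Strengths and limitations** names the small sample as a limitation and does not mention uncontrolled follow-up.

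**The concern.** An effect of the programme is a difference between treated children and what the same children would have scored untreated. To say that an effect is maintained at T4 is to say that this difference is still there at T4. The comparisons listed for maintenance contain only treated children, so they show whether scores stayed low, not whether the programme is why.

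The distinction matters in this trial. The Introduction frames effectiveness as preventing an increase in anxiety symptoms. Flat scores after the programme count as prevention only if untreated children would have risen over the same months, and nothing observed after T2 shows whether they would. Enrolment is universal, irrespective of anxiety level, so stable scores without any programme effect are possible. A rise could equally come from something other than loss of effect.

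Followed as written, the plan could report a durable effect, or a lost one, that the data do not support. The programme is intended as a foundation for later ones, so a durability claim would carry weight.

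**Working it through.** **1. Timeline.** Inputs are 10 sessions at two per week, with the DIG starting straight after the IIG.

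- Programme length: 10 / 2 = 5 weeks, which reproduces the 5 weeks stated under Programme evaluation.
- T1 = week 0; T2 = about week 5; T3 = about week 5 + 5 = 10. A short gap around T2 would shift these slightly, but T2 would remain the last untreated assessment.
- T4 has two stated definitions. Taking 3 months as 13 weeks and 6 months as 26 weeks, T4 is week 10 + 13 = 23 (3 months after the DIG programme) or week 5 + 26 = 31 (6 months after the IIG programme). The two do not agree. That is a separate matter to be reconciled, so both are carried here.
- Untreated share of the T1-T4 window: 5/23 = 22% or 5/31 = 16%. Untreated children at T3 and T4: none.

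**2. What the eight group means can identify.** Let *b* be the common baseline; *n2*, *n3*, *n4* the natural course (change from baseline without the programme) at T2, T3, T4; and *e* a programme effect.

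| | T1 | T2 | T3 | T4 |
|---|---|---|---|---|
| IIG | b | b + n2 + eI2 | b + n3 + eI3 | b + n4 + eI4 |
| DIG | b | b + n2 | b + n3 + eD3 | b + n4 + eD4 |

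- There are nine unknowns. The two T1 cells carry the same information, so the rank is 7.
- Estimable: *b*, *n2* (DIG T2 minus T1) and *eI2* (IIG minus DIG at T2). Not estimable: *n3*, *n4*, *eI3*, *eD3*, *eI4*, *eD4*.
- If the immediate effect is assumed equal in both groups (*eD3* = *eI2*), there are eight unknowns and the rank is still 7. The T3 terms become estimable: *eI3* = (IIG − DIG at T3) + (IIG − DIG at T2). *n4*, *eI4* and *eD4* remain unidentified.
- The IIG-DIG difference at T4 gives *eI4* − *eD4*, the contrast of earlier with later treatment. It gives neither effect alone.

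**3. Illustration (assumed means, not trial data).** Different truths give the same observed means: IIG 50, 45, 45, 45 and DIG 50, 50, 45, 45.

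- *A, effect fully kept.* Untreated level 50, 50, 50, 50; IIG effect 0, −5, −5, −5; DIG effect 0, 0, −5, −5.
- *B, effect gone by T4.* Untreated level 50, 50, 47.5, 45; IIG effect 0, −5, −2.5, 0; DIG effect 0, 0, −2.5, 0.
- *C, effect gone by T4, with equal immediate effects.* Untreated level 50, 50, 50, 45; IIG effect 0, −5, −5, 0; DIG effect 0, 0, −5, 0.

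Adding level and effect gives the same eight means each time (for example IIG at T4: 50 − 5 = 45 in A, 45 + 0 = 45 in B and C). C shows that the equal-effect assumption rescues T3 but not T4.

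**The case against.** The strongest reply is that this is an openly described wait-list design. The article says that both groups are treated, confines the control period to T1 and T2, specifies maintenance as comparisons within groups, and gives the academic year as the reason. Every wait-list trial that treats its controls has this limit. Hypothesis 4 speaks of RCADS results being retained, which is a statement about scores that the data can address. The limitations paragraph does not claim to be exhaustive, and a condensed article may leave more to the full protocol.

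Much of that stands: the design is disclosed, and the limit is inherent rather than careless. But disclosing the schedule is not the same as saying that follow-up is uncontrolled. The third measurable item affirmatively claims that maintenance of the programme's effects can be measured. The point rests on that claim, not on an omission.

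A reader might infer more than the documents support:

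- *That no analysis could recover any later effect.* Too strong. With equal immediate effects the IIG effect at T3 is recoverable. Hypothesis 3 (IIG at T2 against DIG at T3) expresses a related expectation, although a non-significant difference would not establish equality. The comparisons listed for maintenance do not use this route.
- *That the plan relies on about 5 weeks of DIG stability to support 6 months of follow-up.* It lists the two as separate items and never links them. The 16% to 22% describes the schedule, not an inference made by the plan.
- *That the Introduction expects untreated scores to fall.* It says "experiencing transient fears and anxieties is deemed to be a normal part of development for most children", but the same sentence adds that for some children these intensify and persist, and the paragraph says that severe untreated symptoms can become chronic. The direction of natural course is open.

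**Conclusion.** The concern holds in limited form. The article claims a property that the design lacks: at T4 a maintained programme effect cannot be separated from natural course, time of year or repeat testing. At T3 it can be separated only under the assumption of equal immediate effects in the two groups.

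No untreated child is observed after about week 5, whichever T4 definition applies. Any shift in scores after T2 that is unrelated to the programme enters the within-group follow-up change in full, in either direction. Its size cannot be stated, because the documents give no data on untreated course beyond T2, and any figure in standard deviations would be an assumption.

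A reader might infer that the effectiveness evaluation as a whole is undermined. It is not: the randomised IIG-DIG comparison at T2 (hypothesis 2) is untouched, and the follow-up visits still describe how scores run after the programme. What is unsupported is a causal conclusion about durability. The conclusion rests on the schedule as written and on week numbers derived from the 5-week programme.

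**What to change.** 1. **Programme evaluation, third measurable item.** Replace the claim to measure maintenance of the programme's effects with: *course of anxiety scores after the programme, without an untreated comparison*.
2. **Between group effects, hypothesis 4.** Word it as retention of scores within each treated group. Report within-group change with confidence intervals, and do not present it as evidence of a retained programme effect.
3. **Effectiveness conclusion.** State that the causal conclusion rests on the randomised IIG-DIG contrast at T2 (hypothesis 2). Keep the DIG T2 to T3 change and the IIG T2 versus DIG T3 comparison as supportive, uncontrolled analyses.
4. **Strengths and limitations.** Add that follow-up after T2 has no untreated comparison.

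Cost: the durability claim becomes weaker, and hypothesis 4 and the supportive comparisons are reported with a lower standing, which goes slightly beyond wording. Visits, questionnaires and the children's programme do not change, and no new arm is needed.
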